#### Primary outcome

The primary outcome is the mean difference in the goal attainment scale (GAS) score at 6 months over baseline in the intervention arm, compared with the control group [52]. Participants will identify health goals, indicators, and outcomes through structured, prompted discussion. Each participant will rate their progress towards achievement of their goal using a set of five expected outcome levels for each indicator related to that of health goal. Outcome levels identified will be as descriptive, objective, and observable as possible and phrased as relative versus absolute improvements [53]. At 6 months, a GAS score will be calculated for each participant according to conventional methods [52] and used as the primary outcome. The proportion of participants’ self-reporting maintenance or improvement in their top priority goal area will be used as a secondary outcome. Further details about the process for gathering data to create the GAS are provided in Additional file 5.

#### Secondary outcomes

A number of secondary outcomes will be collected (see Tables 2 and 3 for the description and reference of each outcome). Self-efficacy for managing chronic disease [54], quality of life (EQ-5D-5L) [55], optimal aging [56], social support [57], caregiver strain [58], and satisfaction with care will be measured. Also, access to healthcare services received at their clinic, comprehensiveness healthcare services received at their clinic, patient empowerment, and patient-centeredness will be measured using standardized questions developed by the Canadian Institute of Health Information through the Canadian Institutes of Health Research Community-Based Primary Healthcare initiative [59]. Caregiver strain will be measured using the four-item Zarit screen [58]. Hospitalizations and emergency room visits will be categorized into (1) those related to ambulatory care sensitive conditions for chronic disease [60, 61], (2) those related to adverse effects, and (3) overall for any reason.

#### Implementation processes

Qualitative data will be analyzed to help understand the implementation of the intervention including the type and extent of involvement that participants, family caregivers, volunteers, and healthcare team members have in this program, volunteer confidence, and factors influencing implementation of the intervention from the perspectives of all types of participants including factors to consider when adapting the Health TAPESTRY approach to other contexts.

Specifically, the focus group and interview guides for the use with healthcare provider team, volunteers, and client participants will consist of pilot-tested open-ended questions that will address the structures and processes of care, perceived barriers and facilitators of implementing and the use of all components of the intervention, and what worked and did not work in implementing the program and in using each component. The focus group and interview guides are based on normalization process theory [62, 63]. Modifications to the interview guide will occur as themes emerged. Weekly field notes taken during primary healthcare intake team meetings will add rich detail to track the process of implementation of the intervention and any changes made over time. Data will be collected at 3 and 12 months of the intervention. In addition, to maximize Health TAPESTRY’s potential for impact, we assessed the intervention’s sustainability and scalability potential prior to implementation in this current trial using a mixed-methods approach [32]. This work involves (1) administering a sustainability survey (a validated instrument developed by the National Health Service (NHS) institute [64]) to team members who were involved in the intervention development and pilot testing (*n* = 20) and (2) a qualitative study of one-on-one telephone interviews with a subset of NHS survey respondents (*n* = 25) to gain a more in-depth understanding of the factors that influence the implementation, sustainability, and scalability of the Health TAPESTRY intervention. Findings from these studies were used to optimize the intervention in preparation for the current trial [32].

To compliment the qualitative data collected and to further understand the implementation of the intervention and the readiness of healthcare team members for change, quantitative data will also be collected. Organizational readiness of members across MFHT will be measured using the Organizational Readiness for Change Assessment (ORCA) [65]. Time between volunteer completion of data collection, report placement into the EMR, and discussion by intake team will also be recorded and tracked across the trial. The follow-up actions of the healthcare team will be described via chart audit of the EMR. Action type including communication method and the actions made by the healthcare team will be examined. Types of community resources recommended and utilized by participants will also be recorded. Finally, the types of life and health goals generated by participants and the proportion of recommendations made or actions taken to address these goals will be recorded. Other implementation elements complimented by a quantitative measure are volunteers’ self-efficacy to fulfill their role as a volunteer, the completeness of the initial assessments completed by the volunteers during home visits, and PHR uptake and use (see Tables 2 and 3 for descriptions).

#### Adverse events

Details of adverse events or harms from any source will be reported to the research team and recorded on a structured form. Follow-up will be completed by the appropriate person and documented. All critical incidents identified by volunteers, including potential adverse events, will be reported and followed up using a standard protocol.

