## Methods/design

### Design

This is an unblinded delayed intervention pragmatic RCT. Participants in the control group will receive the intervention at 6 months, and both groups will continue to be part of the study until the 12-month mark (Fig. 1). The main analysis will be group comparisons at 6 months. Both groups will be also assessed at 12 months. Ethics approval was granted from the Hamilton Integrated Research Ethics Board (8 December 2014). The trial has been reregistered with Clinical Trials.gov NCT02283723. We used the SPIRIT guidelines to guide reporting of our trial protocol [47].

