### Control

The control group will receive the usual care. These individuals will not have volunteer visits or be discussed at an intake meeting. They may or may not have had a previous PHR account. At the conclusion of the 6-month trial, the control group will have the option of receiving the intervention.

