Demographic information including age, gender, level of education, marital status, ethnicity, language spoken, and number of medications, falls, adverse events, and economic analysis not included in the above table

*T*
_*0*_ baseline, *T*
_*3*_ 3-month collection, *T*
_*6*_ 6-month collection, *T*
_*12*_ 12-month collection

^a^Analyses will be adjusted for participant gender and MFHT site (McMaster Family Practice or Stonechurch Family Health Centre)

**Table 3 Tab3:** Summary of trial client outcomes and implementation processes

Implementation processes			
Variable/outcome	Outcome measure	Timing	Methods of analysis
Volunteer self-efficacy	3-item self-efficacy rating of communication with client, performance of tasks necessary for home visit (i.e., navigate TAP-App) and handling unexpected issues (0–100 % scale)	Prior to each home visit	Mean differences for the first 3 months of visits compared to the second 3 months of visits
Completeness of TAP-App used by volunteers	Time to complete each module; number of items missed	*T* _6_, *T* _12_	Mean differences where applicable
Client satisfaction with volunteers	Description of experience with volunteer home visits	*T* _3_, *T* _12_	Qualitative descriptive method
Uptake of personal health record by clients	PHR metrics including number of times logged in, features used, number of secure messages sent, issues encountered, and described experience with the personal health record	*T* _0_, *T* _6_, *T* _12_	Mean differences where applicable; content analysis with frequency counts of each category where applicable
Type and extent of healthcare team involvement with client	Chart audit to track actions of healthcare team (type of follow-up, team members involved)	*T* _6_	Content analysis with frequency counts of each category of resource
Quality and extent of healthcare team functioning and organizational readiness for change by health team members	Described in qualitative interviews	*T* _3_, *T* _12_	Qualitative descriptive method
	ORCA [66]		Mean difference between *T* _3_ and *T* _12_
How often and what types of community resources are utilized by clients?	Chart audit to track connections to community resources and programs	*T* _6_	Content analysis with frequency counts of each category of resource
Type and extent of involvement of clients in program	Described in qualitative interviews	*T* _6_	Qualitative descriptive method

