#### Client outcomes

We propose to test using two analysis sets: ITT set, considering all patients as randomized regardless of whether they received the intervention and a “per protocol” analysis set. A per protocol analysis will include all participants who received the intervention including both members of a couple assigned to the intervention group compared with all participants randomized to the control group including both members of a couple assigned to the control group.

Quantitative data analysis will include descriptive analyses with means and standard deviations calculated for the continuous variables and frequencies calculated for categorical variables. Data will be summarized in tabular or graphical form. The main between-group comparison will take place at 6 months. This point also serves as the control group’s baseline as they move into the intervention arm based on the delayed design. The comparison at 12 months then compares the effect of the intervention after 12 months of participation (original intervention group) versus 6 months of intervention (original control group).

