Interventions and expertise	Experimental intervention-flexibility	TAP-reports reviewed and action plan is developed for that particular person based on their individual self-report information so action plans are all different. There is not a “one size fits all” approach to reports. No specific instructionsgiven to intake teams on process, allowed teams to develop own process and workflow for TAPESTRY; practice was allowed to be different between the two clinics. Never forced clients to use PHR to facilitate connection to healthcare team. At least one home visit by the volunteer was initiated, but no minimum or maximum follow-up visits were enforced in the trial	5
	Experimental intervention-practitioner expertise	MFHT and intake teams made up of different people, intake teams changed throughout the trial, elements of care plan carried out by various MFHT members, regardless of level of expertise	5
	Comparison intervention-flexibility	Control individuals allowed to receive any type of care from any healthcare professional at the clinic. Individuals in the control group do not receive volunteer visits, the TAP-App and are not discussed at the intake team meetings	5
	Comparison intervention-practitioner expertise	Same MFHT members are involved in the care of individuals in the intervention and control groups	5
Follow-up and outcomes	Follow-up intensity	Formal follow-up to collect research outcomes (baseline, 6 and 12 months). No formal volunteer home visit follow-up schedule of clients, no instruction for MFHT of clinic follow-up	4
	Primary trial outcome	Primary out is GAS score, which is subjective, person-centered care outcome and clinically meaningful to client	5
Compliance/adherence	Participant compliance with “prescribed” intervention	No formal strategy to encourage compliance; methods to encourage use of PHR, improve volunteer confidence in role	5
	Practitioner adherence to study protocol	Only subtle strategies to encourage intervention to move forward have left for organic process, but no formal strategy to monitor adherence or encourage adherence; researchers sat in intake team meetings early on to track development of processes, however, have withdrawn researchers have intake teams to lessen influence of initiative	4
	Analysis of primary outcome	Using intention to treat principle, intention to include all experiences in evaluation (good and bad), statistical analysis plan will work under “noise”	5

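### Before 6 months only the intervention arm has volunteers who can report adverse events, so any by-arm summary of those reports would lean against the programme

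*Protocol article*

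**What the plan says.** The Adverse events section, under Outcomes, has two parts. The general rule is open to both arms: "Details of adverse events or harms from any source will be reported to the research team and recorded on a structured form". The second part names a particular reporter: "All critical incidents identified by volunteers, including potential adverse events, will be reported and followed up using a standard protocol".

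Volunteer contact belongs to the intervention. The Control section says "These individuals will not have volunteer visits or be discussed at an intake meeting", and Table 4 in the Discussion repeats it: "Individuals in the control group do not receive volunteer visits, the TAP-App and are not discussed at the intake team meetings". Within the intervention arm the amount of contact is left open: "At least one home visit by the volunteer was initiated, but no minimum or maximum follow-up visits were enforced in the trial".

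On timing, the Design section states "Participants in the control group will receive the intervention at 6 months", and the Client outcomes part of Data analysis states "The main between-group comparison will take place at 6 months".

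Adverse events and falls appear in the notes to Tables 2 and 3 among the items left out: "number of medications, falls, adverse events, and economic analysis not included in the above table". The article gives no hypothesis, time point or model for them by name.

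**The concern.** One arm has an extra pair of eyes in the home and the other does not. A fall or drug reaction in an intervention participant can reach the research team through the general route or through a volunteer. The same event in a control can reach it only through the general route. The article describes no scheduled adverse event question that would give controls a matching opportunity.

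If the reports were counted by arm, equal true rates would look like an excess with the programme, and a real reduction could be hidden. This cannot be repaired at the analysis stage. Control events that nobody collected cannot be recovered, and volunteer reports can be separated out only if the source of each report was recorded. The primary outcome, goal attainment, is not affected.

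**Working it through.** **Is the route confined to one arm?** Setting the sections side by side:

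- Adverse events: volunteer-identified incidents, including potential adverse events, are reported.
- Control and Table 4: controls have no volunteer visits, no TAP-App and no intake review.
- Design: controls cross over at 6 months.
- Client outcomes: the main comparison is at 6 months.

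From randomisation to the main comparison, the volunteer route therefore has no counterpart in the control arm. Its yield within the intervention arm also depends on the number of visits, which is not fixed beyond the first. After 6 months the imbalance shrinks but remains in cumulative counts, because the 12-month comparison sets 12 months of intervention against 6.

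**How large could the effect be?** The plan has no harms figure to reproduce: it gives no adverse event rate, capture rate or power for harms. Its sample size of 286 (316 with allowance for loss) concerns the goal attainment score and plays no part here. The following is an illustration on assumed inputs.

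Let p be the true event rate, equal in both arms. Let c be the share of events caught by routes common to both arms, and v the share of the remaining events caught by volunteers, in the intervention arm only.

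- Recorded rate, control: p × c
- Recorded rate, intervention: p × [c + (1 − c)v]
- Recorded ratio: [c + (1 − c)v] / c = 1 + v(1 − c)/c

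The true rate p cancels.

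| c (assumed) | v (assumed) | Recorded ratio when the true ratio is 1 |
|---|---|---|
| 0.5 | 0.2 | 0.60/0.50 = 1.20 |
| 0.5 | 0.4 | 0.70/0.50 = 1.40 |
| 0.8 | 0.2 | 0.84/0.80 = 1.05 |
| 0.8 | 0.4 | 0.88/0.80 = 1.10 |
| 0.9 | 0.1 | 0.91/0.90 = 1.01 |
| any | 0 | 1.00 |

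A less favourable pair, c = 0.4 and v = 0.5, gives 1 + 0.5 × 0.6/0.4 = 1.75. The size is thus set by the assumptions. The direction is not: whenever v is above 0 and c below 1, the ratio exceeds 1.

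The same factor multiplies a true effect. At c = 0.5 and v = 0.2, a true ratio of 0.83 would be recorded as 0.83 × 1.20 = 1.00, so the reduction would vanish.

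**Which harms data are free of this?** Hospitalisations and emergency room visits, including a category for those due to adverse effects, are secondary outcomes abstracted from the EMR at baseline, 6 and 12 months (Table 2 and Secondary outcomes). The abstraction form is structured and pilot-tested, with duplicate abstraction until kappa reaches 0.70 (Client outcome measures). Volunteer incident reports do not feed this measure. One caution: the caption to Fig. 2 says that Health TAPESTRY reports are uploaded into the EMR. An abstractor who reads them could have more information for intervention participants when deciding whether a visit was due to an adverse effect.

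**The case against.** The strongest reply is that the article announces no harms comparison. The Outcomes section promises only a description of how adverse events are tracked, and the Adverse events section deals with recording and follow-up, which serves participant protection. Adverse events are not in the list of secondary outcomes. Tabulation of safety data is normally left to the full protocol or analysis plan, neither of which is shown. This stands, and it makes the point conditional on a by-arm summary being produced. The condition is not remote: adverse events sit under Outcomes, and the analysis text applies its between-group model to all outcomes.

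Second, the general rule accepts reports from either arm, and the EMR measure covers events serious enough to lead to an admission or emergency visit. This also stands. It leaves the falls and reactions that lead to neither, for which the opportunity to be noticed still differs by arm.

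Third, the size is wholly assumed. The volunteer route concerns critical incidents, and as little as one visit is assured, so v could be well below 0.2. That is correct, and it is why the lower end of the range is near 1.0.

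A reader might infer more than the documents support:

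- *That adverse events rest on volunteer reports alone, or that no valid statement on harms is possible.* The general form and the EMR outcomes contradict this.
- *That adverse events are the only outcome without scheduled collection, because they are left out of Table 2.* The same note leaves out demographics, medications and the economic analysis, so it reflects table layout. Nor is baseline, 6 and 12 months universal in Table 2: goal attainment is listed at 6 and 12 months only. The full protocol or additional files may contain adverse event questions.
- *That volunteers actively solicit adverse events.* The text has them report what they identify and describes no questioning.

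**Conclusion.** The point holds in limited form. Up to 6 months, ascertainment of adverse events is unequal by arm, because a named reporting route exists in the intervention arm only and varies there with the number of visits. The article does not state an explicit between-arm test of these reports, so no planned inference is shown to be wrong. Any by-arm summary of them would, however, be biased against the programme. The amount cannot be calculated from the documents. With shared routes catching 50% or more of events and volunteers catching up to 40% of the rest, the spurious ratio runs from near 1.0 to about 1.4. Those capture rates are assumptions, as is equal performance of the shared routes in both arms. The primary outcome and the EMR-based utilisation outcomes do not depend on the volunteer reports. This is an inexpensive improvement worth making, not a flaw in the main analysis.

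**What to change.** In the Adverse events section, add that:

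1. Any between-arm summary of harms covers randomisation to 6 months and uses only sources applied identically to both arms. These would be the same short adverse event and falls questions, asked by researchers at the existing 6-month contact, and EMR abstraction that does not draw on the uploaded Health TAPESTRY reports.
2. The structured form records the source of each report.
3. Volunteer-identified incidents are listed separately and descriptively, outside the comparison.

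Volunteer reporting and the follow-up of incidents remain unchanged. If matching questions already exist in the full protocol, items 1 and 3 need only a sentence each.

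The cost is a few questions at a contact that already takes place in both arms, one field on the form, and a short addition to the text. The drawbacks are slightly longer contacts and fewer events in the comparative table.

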#### Cost-effectiveness

Incremental costs and effects (utility) will be calculated and if the Health TAPESTRY program is both more costly and more effective, an incremental cost-utility ratio will be calculated showing how much more it costs for a QALY gained, using EQ-5D-5L [55] as the indicator of quality of life. If the Health TAPESTRY program is equally effective as no Health TAPESTRY program, then the economic evaluation will be based solely on incremental costs (see Additional file 6 for full details).

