#### Econosmic analysis

The economic analyses will include program cost measures, health resource use and cost, and patient quality of life. The cost-effectiveness/utility analysis will be conducted from the Ontario government healthcare system perspective.

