#### Power and sample size

Assuming baseline scores of 30 on the GAS score in intervention and control groups and a standard deviation of 15 with a power of 80 % and type I error probability of 0.05, we will need to enroll 286 patients overall to detect a mean difference of 5 points on the GAS score representing improvement in the level of goals attained in the intervention group compared with control [71–73]. Previous studies in older adults have demonstrated that this difference indicates a meaningful change in effect and is achievable [71–73]. This sample size will also give sufficient power to detect a difference of 1.0 (SD, 2.5) on the self-efficacy for managing chronic disease scale [54] and a difference of 0.10 (SD, 0.3) on the EQ-5D-5L measure, both identified as meaningful differences. The study will not be powered for planned subgroup analyses, and so these will be considered exploratory. To account for a 10 % potential loss to follow-up in the study, we will aim to enroll 316 participants.

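### The economic evaluation falls back to costs alone on a finding of equal effectiveness that the article does not define and the trial is not sized to show

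*Protocol article*

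**What the plan says.** The Cost-effectiveness section (under Outcomes) begins without a condition: "Incremental costs and effects (utility) will be calculated". Two conditional rules follow. The first is that "if the Health TAPESTRY program is both more costly and more effective, an incremental cost-utility ratio will be calculated", with EQ-5D-5L supplying the quality-of-life weight. The second is: "If the Health TAPESTRY program is equally effective as no Health TAPESTRY program, then the economic evaluation will be based solely on incremental costs". The section then points elsewhere: "see Additional file 6 for full details". That file is not among the documents at hand.

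The economic subsection of Data analysis lists programme cost, resource use and cost, and quality of life as components, and adds: "The cost-effectiveness/utility analysis will be conducted from the Ontario government healthcare system perspective".

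Table 2 has EQ-5D-5L collected at baseline, 6 and 12 months. The Client outcomes part of Data analysis reports effects as estimates with 95% confidence intervals and p values, adjusted for baseline scores.

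Power and sample size assumes "a standard deviation of 15 with a power of 80 % and type I error probability of 0.05" and concludes that "we will need to enroll 286 patients overall to detect a mean difference of 5 points on the GAS score". It says the same size suffices for "a difference of 0.10 (SD, 0.3) on the EQ-5D-5L measure, both identified as meaningful differences".

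**The concern.** Two estimated QALY means will practically never be equal, so a rule triggered by equal effectiveness needs a working criterion. The article supplies none: no measure, margin or test is named. The design does not supply one implicitly either, because the EQ-5D-5L figure in the power section is a difference to be detected, not a margin within which the arms would count as equal.

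If the costs-only branch is taken, the estimated QALY difference and its uncertainty no longer enter the economic conclusion. A volunteer-based programme has delivery costs. It could be reported as not worthwhile on cost grounds while the data remain compatible with a QALY gain that the payer would value. It could equally be reported as cost-saving while the data remain compatible with a QALY loss. What matters is how wide that remaining uncertainty is at the planned size.

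**Working it through.** **Inputs from the article (Power and sample size):** GAS difference 5, SD 15; EQ-5D-5L difference 0.10, SD 0.3; power 80%; type I error 0.05; 286 patients overall. **Assumptions:** two-sided test and 1:1 allocation (neither is stated), so 143 per arm.

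**1. Reproducing the plan's figure.** Normal approximation: n per arm = 2 × [15 × (1.960 + 0.842) / 5]² ≈ 141.3, rounded up to 142, or 284 in total. The t-based calculation gives 79.9% power at 142 per arm and 80.2% at 143, so 286 is reproduced. The EQ-5D-5L target has the same standardised size (0.10/0.3 = 5/15 = 1/3) and so the same power, 80.2%. The stated sample size is sound for detecting differences.

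**2. Precision of the utility difference.**
- SE = 0.3 × √(2/143) = 0.0355
- 95% half-width = 1.96 × 0.0355 = 0.0695, about 0.07

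This is before baseline adjustment. With an assumed baseline correlation of 0.5 it becomes 0.0695 × √(1 − 0.25) = 0.060.

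**3. Conversion to QALYs over 6 months** (unadjusted; the path over time is an assumption).
- Difference builds linearly from zero: 0.0695 × 0.5 year × ½ = 0.0174
- Difference held throughout: 0.0695 × 0.5 year = 0.0348

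**4. Value per person** (thresholds assumed; the article gives none).

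| Threshold per QALY | Linear build-up | Held throughout |
|---|---|---|
| 20,000 | ±348 | ±695 |
| 50,000 | ±869 | ±1,738 |
| 100,000 | ±1,738 | ±3,477 |

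**5. Could the trial show equality formally?** Use two one-sided 5% tests with a true difference of zero and margins m that are assumptions. Power at 143 per arm = 2Φ(m/0.0355 − 1.645) − 1, taken as zero where negative. The n per arm for 80% power = 2 × [0.3 × (1.645 + 1.282)/m]².

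| Margin m | Power at 143 per arm | n per arm for 80% power |
|---|---|---|
| 0.10 | 76% | 155 |
| 0.07 | 26% | 315 |
| 0.05 | 0% | 617 |

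Only a margin as wide as the difference the plan itself calls meaningful comes near conventional power.

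**The case against.** The strongest reply is that the section is a summary that expressly defers to Additional file 6. A criterion for equality, the treatment of other cost and effect combinations, and methods for uncertainty could all be there. That stands as far as it goes, and it rules out three stronger readings.

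- A reader might infer that a non-significant difference will be taken as equality. The article names no test in this rule, and a margin or a confidence interval could serve as well.
- A reader might infer that QALY uncertainty is ignored throughout. Incremental effects are to be calculated in any case, and EQ-5D-5L is a secondary outcome reported with a confidence interval. Only the conclusion of the costs-only branch leaves this uncertainty out.
- A reader might object that a programme both cheaper and less effective is not covered. That cannot be verified without the file, and restricting the ratio to the more costly, more effective case is largely conventional.

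The deferral does not remove the rule itself. The switch to costs alone is a stated analysis choice, and it remains unless the file reverses it.

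A second reply is that ±0.07 around zero excludes the 0.10 that the plan calls meaningful, and that baseline adjustment will narrow it further. Both are true. But the exclusion holds only close to zero: without adjustment, an observed difference of 0.10 − 0.0695 = 0.0305 already puts 0.10 at the limit of the interval. Moreover, 0.10 was chosen as a difference to detect. Whether a smaller gain matters to the payer depends on what the programme costs, and a costs-only evaluation never makes that comparison.

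**Conclusion.** The point holds, as a modest one. The article fixes a rule that drops the QALY difference from the economic conclusion when effectiveness is judged equal. It gives no criterion for that judgement, and the trial is sized to detect differences. The uncertainty set aside is about ±0.07 in utility before baseline adjustment, or ±0.017 to ±0.035 QALY per person over 6 months. In money this is roughly ±350 to ±3,500 per person across assumed thresholds of 20,000 to 100,000 per QALY.

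These figures rest on the plan's SD of 0.3, 1:1 allocation with 143 analysed per arm, an observed difference of zero, and the two assumed paths of the utility difference. Additional file 6 could supply a criterion for equality. A criterion alone would not cure the problem, because the trial has little or no power for margins clearly tighter than 0.10.

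**What to change.** Delete the sentence that makes the evaluation rest on costs alone. State instead that, whatever the effect result:

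- incremental costs and incremental QALYs will be estimated jointly from randomisation to 6 months, with QALYs adjusted for baseline EQ-5D-5L;
- incremental net benefit will be reported with bootstrap intervals, resampling each participant's costs and QALYs together, and with an acceptability curve over a stated range of thresholds;
- the cost-utility ratio will be given only where it is interpretable.

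If Additional file 6 already provides this, the article's sentence should be brought into line with it. The EQ-5D-5L data at baseline and 6 months and the cost data are already planned, so the cost is a change of wording and a little more analyst time.
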